### Performance and measures: trunk-raising test (TR: how and when)

A. The TR test does not require any instruments. The examiner evaluates whether the supine patient (hips flexed 45° and knees at 90°) is able to perform some simple exercises that are scored for points (maximum 5 points). The score for this test is determined by the arm position the patient uses to elevate the scapulae off the table and how long the patient is able to hold this position.

••Hands behind neck, scapulae clearing the table, 20” hold (normal), 5 points.

••Arms crossed over the chest, scapulae clearing the table, 20” (good), 4 points

••Arms straight, scapulae clearing the table, 10” hold (fair), 3 points

••Arm extended toward the knees, top of scapulae lifting from the table (poor), 2 points

••Inability to raise more than the head off the table (trace), 1 point

B. The test will be performed preoperatively and at 1 month, 6 months and 12 months postoperatively.

### Abdominal wall strength (AWS) score

A. We will obtain the AWS score by summing the results of the DLL and TR tests. The AWS score ranges from 0 to 10 points.

B. The test will be performed preoperatively and at 1 month, 6 months and 12 months postoperatively.

### Quality of life

A. It appears appropriate for the purpose of the study to use the Medical Outcome Study Short Form-36 (SF-36) Health Survey. This is a comprehensive assessment of overall health status encompassing physical, emotional and mental life aspects over a predefined period of time [26,27]. It is a multidisciplinary questionnaire composed of 36 items that determine the health-related quality of life [28]. Before surgery, the generic quality of life will be prospectively measured using the Medical Outcome Study SF-36 Health Survey, which is composed of eight different health-quality domains: physical and social functioning (PF and SF, respectively), body pain (BP), general health perception (GH), physical and emotional role limitations (RP and RE, respectively), vitality (VT) and mental health (MH). The scores for each domain range from 0 to 100, with higher scores indicating better quality of life.

The score has been already extensively validated and adopted in clinical practice and in the field of abdominal wall hernia surgery [16,29,30].

B. The SF36 will be administered preoperatively and at 1 month, 6 months and 12 months postoperatively.

### Scoring for pain

A. A visual analog scale (VAS) will be used for patient pain evaluation. As the name implies, VAS uses an analog format, meaning that it represents a continuous range of values [31,32]. The most common style used in pain measurement uses a horizontal line measuring exactly 10 cm (100 mm). The patient is asked to make a mark on this line, and then the line is measured and recorded in millimeters or centimeters (e.g., 37 mm or 3.7 cm). The length of the line is important for this outcome measure because this tool has been evaluated in this format, and the measurement relies on the line being exactly 10 cm long. The scale is formatted without numbers.

B. Measures of VAS will be taken preoperatively, postoperatively on day 1, the day of discharge and 10 days, 6 and 12 months postoperatively.

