Very little evidence [6,7] and recently a large prospective trial [8] comparing laparoscopic and open techniques in terms of a quality of life (QOL) measurement tool specific for hernia outcome study (the Carolina Comfort Scale) have indicated a possible benefit in the short term granted by the open fascial closure of the abdominal defect. Basing their assumption on these observations and on the equivocal results on QOL from trials comparing laparoscopic and open ventral hernia repair [9,10], experts in the field [11,12] have hypothesized that medialization of the rectus abdominis muscles improves abdominal wall function. This speculation has not been objectively proven because measures of the recurrence rate, quality-of-life scores and patient questionnaire responses remain the only established criteria for assessing abdominal wall function after hernia repair. Nevertheless, expert groups recommend this approach for ventral hernia repair as a rule to centralize and re-approximate the rectus muscles along the midline to the extent possible. This step attempts to restore the functional, innervated abdominal wall and perform dynamic reparation without undue tension. Commonly used techniques with the aforementioned characteristics that have been used for the repair of abdominal hernias include retrorectus (i.e., the Rives-Stoppa procedure) and component separation (the Ramirez technique). Thus, several surgeons consider these the current “gold standard” treatments.

Based on this assumption, even if laparoscopic surgery has gained an adequate scientific consensus for the surgical treatment of different diseases [13,14], certain criticisms have been raised over its introduction in the routine practice of abdominal hernia repair. These techniques, which avoid the restoration of anatomical integrity for a simple bridging of the defect, appear “less effective.”

Nevertheless, a recent systematic review of studies comparing laparoscopic and open techniques [15] was not able to confirm this assumption. On the contrary, the review indicated that laparoscopic incisional hernia repair is generally safe, with a lower risk of wound infection and shorter hospital stays relative to open surgery.

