To compare the DLL test results during follow-up between the two groups of treatment, ANOVA for repeated measures will be adopted using DLL as the dependent variable. Because the DLL test cannot have a normal distribution, a ranking transformation will eventually be used. The same approach will be used for the other ordinal characteristics used as secondary outcomes (VAS as scoring for pain and AWS score) and, in general, for all other outcomes considered. If a consistent number of missing values is detected during the follow-up, ANOVA for repeated measures will be replaced by linear mixed or generalized estimating equation (GEE) models, which permit the exclusion of the data only from a single missing observation and not from the patient on overall as with ANOVA. Single comparisons between baseline values and each time during follow-up will be assessed using Bonferroni correction for multiple comparisons. All analyses will be performed on an intention-to-treat basis. A *p*-value lower than 0.05 will be considered statistically significant. SPSS (v.20, IBM Corp., Armonk, NY, USA) will be used for the statistical analyses.

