### Postoperative

Postoperative pain control is planned with the elastomeric pump infusion of painkillers. Parenteral opioids will be used for rescue analgesia. Patients will be allowed liquids on the night of surgery, a semisolid diet on the first postoperative day and a light meal on the second. In case of unplanned resection, the decision will be left to operating surgeon. Patients will be discharged when they are conscious and orientated, able to tolerate a solid diet, have regular bowel functions and are able to take care of themselves.

Postoperative medications:

Low-molecular-weight heparin will be prescribed for deep venous thrombosis and pulmonary embolism prophylaxis. Painkillers and antibiotics will be prescribed based on the patient’s needs. Patients will also be prescribed a post-surgical belt for 30 days to minimize seroma formation.

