### Follow-up

The patient will be submitted to a 1-year postoperative follow-up. Planned follow-up visits will be on the following days:

•10 ± 3 days (wound evaluation and clinical evaluation)

•30 ± 3 days (clinical evaluation and study test performance)

•180 ± 3 days (clinical evaluation and study test performance)

•360 ± 3 days (clinical evaluation and study test performance)

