**Figure 1 F1:**
[figure not shown]
Jamar E-Z Read Goniometer 12/32 cm.

To obtain a more precise and less variable measurement, before performing the test, three colored dots will be applied to the hip and ankle of the patients and on the underlying surface. During the test, a picture of the patient will be shot at maximum leg rise. Using the dots as reference points, the angle will be measured with computer software directly on the picture.

After measuring the angle, a score will be assigned for the calculation of AWS (5 points).

B. The test will be performed preoperatively and at 1 month, 6 months and 12 months postoperatively.

•41° or more (normal) 5 points

•31°-40° (good) 4 points

•21°- 30° (fair) 3 points

•11°-20° (poor) 2 points

•0°-10° (trace) 1 point

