### Clinical implications

Given the constant and equal number of recurrences in both groups, if patients submitted to laparoscopic repair have the same results in physical testing in comparison with open repair, then the trial would indicate (*acceptance of the null hypothesis*) that an anatomic repair of incisional hernia through rectal muscles medialization does not offer any advantage to the patient. The reasons for this deduction could be twofold: first, the anatomic repair is not effective on previously scarred tissue, and, second, the dimensions of the defect included in this trial are too small to determine a perturbation of the abdominal motility. The clinical implications for these results would be that the laparoscopic bridging hernia repair in patients over 60 years of age should be considered a valid alternative to open repair, for both its efficiency and functional, or even superior, results given the advantages already demonstrated in previous trials (fewer wound complications, shorter postoperative hospital stay). It would remain an open question whether the restoration of the anatomic abdominal structure would be useful in younger patients. If the results reveal a better test performance in the anatomic reconstruction group (*rejection of a null hypothesis*), the choice of this type of intervention as the gold standard technique would be supported by clear evidence of an advantage offered in terms of the functional restoration of the abdominal wall.

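### The discharge-day VAS reading is not at a common postoperative age in the two arms and should stay out of the repeated-measures model; VAS is also not scheduled at the 1-month DLL/TR visit

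*Protocol article*

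**What the plan says.** Scoring for pain sets six VAS occasions: "Measures of VAS will be taken preoperatively, postoperatively on day 1, the day of discharge and 10 days, 6 and 12 months postoperatively". Four of the five postoperative occasions have a nominal time; the discharge reading does not.

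The Postoperative section makes discharge depend on recovery: "Patients will be discharged when they are conscious and orientated, able to tolerate a solid diet, have regular bowel functions", together with the ability to care for oneself. On stay by technique, the Background cites a systematic review that found laparoscopic repair to come "with a lower risk of wound infection and shorter hospital stays relative to open surgery". Clinical implications counts among the advantages of laparoscopy shown in previous trials "fewer wound complications, shorter postoperative hospital stay". Neither place gives a number of days.

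The statistical analysis section specifies repeated-measures ANOVA for DLL, with a rank transformation if needed, and extends the same approach to the ordinal secondary outcomes, named as "VAS as scoring for pain and AWS score". It adds Bonferroni-corrected comparisons of baseline with each follow-up time.

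Follow-up lists a visit at "30 ± 3 days (clinical evaluation and study test performance". For DLL the article says "The test will be performed preoperatively and at 1 month, 6 months and 12 months postoperatively", and the same schedule is given for TR and AWS. For quality of life: "The SF36 will be administered preoperatively and at 1 month, 6 months and 12 months postoperatively". VAS is not listed at 1 month. Pain appears among the secondary outcomes without time points.

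**The concern.** A repeated-measures comparison of two arms at a given level is readable as a treatment effect when that level means the same time since surgery in both arms. The discharge level is defined by an event that follows treatment and that the article's own sources place earlier after laparoscopy. Randomization does not balance it, because the timing is itself a consequence of the allocated operation. If pain is falling over those days, two arms with equal pain on equal days would show different VAS at discharge. Nothing in the stated analysis takes account of the day on which the reading was made.

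The second part is a gap in the schedule. DLL and TR are effort tests, and the arms differ in access and mesh fixation, so pain is a plausible arm-related limit on performance soon after surgery. DLL, TR and AWS at 1 month are declared secondary outcomes, yet the trial's own pain instrument is not used at that visit. A 1-month strength difference would be harder to interpret without a pain score taken at the time of the test.

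**Working it through.** There is no stated figure to reproduce on this point. The sample size rests on DLL alone and does not depend on the pain schedule. The check is a comparison of schedules followed by an illustration.

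**1. Schedules side by side** (from Scoring for pain, the DLL, TR and AWS sections, and Quality of life)

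| Occasion | VAS | DLL, TR, AWS | SF-36 (includes body pain) |
|---|---|---|---|
| Preoperative | yes | yes | yes |
| Day 1 | yes | no | no |
| Day of discharge | yes, day not fixed | no | no |
| Day 10 | yes | no | no |
| 1 month (30 ± 3 days) | **no** | yes | yes |
| 6 months | yes | yes | yes |
| 12 months | yes | yes | yes |

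- Early postoperative VAS readings: day 1, discharge, day 10. One of the three has no common postoperative day.
- Strength-test occasions without a VAS: 1 month only. SF-36 body pain is collected there.
- Interval without a VAS: from day 10 to day 180, 180 − 10 = 170 days. It contains one strength-test visit. It is not an interval without any pain data, because SF-36 body pain falls inside it.

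**2. What the discharge comparison estimates**

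Let *b* be the average fall in VAS per day around discharge, and *d* the number of days by which laparoscopic patients leave earlier. If the arms have equal pain on equal days, the difference seen at discharge (laparoscopic minus open) is

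artefact = *b* × *d*.

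Neither input is in the documents. With assumed values *b* = 2, 5 or 8 mm per day and *d* = 1, 2 or 3 days:

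| | *d* = 1 | *d* = 2 | *d* = 3 |
|---|---|---|---|
| *b* = 2 | 2 mm | 4 mm | 6 mm |
| *b* = 5 | 5 mm | 10 mm | 15 mm |
| *b* = 8 | 8 mm | 16 mm | 24 mm |

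So 2 to 24 mm on a 100 mm scale, with the earlier-discharged arm looking worse. This shows how the artefact scales; it is not an estimate for this trial.

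**3. Why the net direction is open**

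The table holds only if discharge timing is unrelated to pain. Discharge criteria select patients in a similar state of recovery. To the extent that pain moves with recovery, patients are scored at similar pain whatever their day. That shrinks the artefact and would also hide a true difference between arms. The criteria do not name pain, so how far this goes is unknown.

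**4. Effect of the fix on the number of levels**

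Now there are five postoperative levels: day 1, discharge, day 10, 6 and 12 months. After the change there are also five: day 1, day 10, 1, 6 and 12 months. If every follow-up level is compared with baseline, the Bonferroni threshold is 0.05/5 = 0.01 either way.

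**The case against.** The case for leaving the plan alone has several sound parts.

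- *Two of the three early readings are clean.* Day 1 and day 10 are common to both arms and give an early comparison free of the timing problem. A reader might infer that early pain as a whole is compared at different postoperative ages. The schedule does not support that; the problem is confined to discharge.
- *Pain is measured at 1 month.* SF-36 is given at that visit and has a separately scored body pain domain (0 to 100). A reader might infer that the 1-month strength test has no pain reading at all. Only the VAS is missing. The SF-36 is a partial substitute, because the article describes it as covering a predefined period and not the moment of the test.
- *The article cites contrary evidence.* The Background reports a randomized trial in which pain and recovery at 3 weeks did not differ by type of repair. This weakens the expectation of arm-related pain at day 30, but does not show it is absent in this trial.
- *The coding of time is not spelled out.* The article says the DLL approach will be used for VAS without listing which occasions enter the model, and an analysis plan not shown may settle this. That stands as a limit on the point. Still, the article fixes both the reading and the type of model and gives no sign that discharge is handled differently.
- *Pain at discharge is a legitimate milestone.* Agreed. The point is how it is analysed, not that it is collected.

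**Conclusion.** The point holds in limited form. One of three early VAS readings is tied to a criterion-based event that the article's own sources place earlier after laparoscopy. As a common level of the repeated-measures model, it would confound time since surgery with treatment at that reading. The 1-month visit is the only DLL/TR occasion without a VAS, partly covered by SF-36 body pain.

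The size cannot be derived. The 2 to 24 mm range rests wholly on assumed rates of pain decline and assumed differences in stay. It is tempting to conclude that the reading is biased against laparoscopy by a known amount. The documents do not support this: they give no stay in days and no pain trajectory, and selection by recovery state works against the simple timing effect.

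The consequence is modest. Pain and 1-month strength are secondary outcomes. The 12-month DLL primary outcome has a VAS at the same visit, and neither it nor the sample size is affected. The change is worth making because it is nearly free.

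**What to change.** 1. Base the between-arm VAS model on the fixed occasions only: baseline, day 1, day 10, and 1, 6 and 12 months.
2. Keep the discharge VAS, but report it descriptively by arm, together with the postoperative day on which it was taken.
3. Add a VAS at the existing 30 ± 3 day visit, completed before the DLL and TR tests.

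The cost is one extra 100 mm line per patient at a visit that already takes place, and one fewer early level in the model (two instead of three). No extra visit is needed, and discharge criteria, treatment, sample size and primary analysis stay as they are.

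Replacing the discharge reading by a fixed early day with a take-home form is a more debatable option. If one arm leaves hospital sooner, more of its scores would be completed at home and more might be missing, so setting and missingness could then differ by arm. The three steps above avoid that.

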### Performance and measures: intrabdominal pressure (IAP: how and when)

A. Patients will be submitted to evaluation of intraabdominal pressure (IAP) according to current guidelines [33]. IAP is the pressure concealed within the abdominal cavity and should be expressed in mmHg and measured at end-expiration in the complete supine position after ensuring that abdominal muscle contractions are absent and that the transducer is zeroed at the level of the mid-axillary line. The reference standard for intermittent IAP measurement is via the bladder with a maximal instillation volume of 25 ml of sterile isotonic saline (normal IAP is approximately 5–7 mmHg in critically ill adults).

B. Patient IAP will be assessed preoperatively, at the end of the surgical procedure (curarized) and on the first postoperative day, before catheter removal.

### CT scan

A. Patients will be submitted to a CT scan to evaluate the size of the defect and decide the final enrollment into the study in the preoperative phase. The CT requirement is a scan able to produce images with 1.2 isometric voxels.

B. CT scans will be performed preoperatively and 12 months postoperatively to rule out recurrences, evaluate interrectal distances and evaluate the volumetry of the abdominal cavity with correlation to preoperative values.

### Respiratory function evaluation

A. Pulmonary function tests will be interpreted by a pulmonologist who is blind to the study and its participants. Forced vital capacity (FCV) and forced expiratory volume (FEV1) will be measured. Intraoperative peak airway pressures, measured at the end of the inspiratory phase of each breath, will be automatically calculated by the mechanical ventilator and recorded by the anesthesiologist prior to opening the abdomen, while the abdomen is open, after rectus muscle plication and after skin closure.

B. Spirometry will be performed on all patients during the preoperative visit and then 6 or 12 months postoperatively.

### Recurrence

A. Recurrence is defined as any postoperative bulging in the area of the edge of the mesh.

B. At each postoperative visit, each patient will be examined by an independent surgeon to determine the presence or absence of recurrence. Recurrences detected clinically will be confirmed by computed tomography of the abdomen or during a second operation.

### Postoperative complications definition and grading

To evaluate postoperative complications and standardize their reporting, we decided to use the classification introduced by Dindo and coworkers in 2004 [34].

### Data collection

Data will be gathered at each single unit for each single subject by filling out the provided Case Report Form (CRF). The original CRFs of all participants will be kept in the unit in which the patients undergo the surgical procedure. A copy of the CRF will be transmitted (either scanned and e-mailed or copied and mailed by traditional mail) to the University of Genoa Department of Surgery and Integrated Diagnostics (DiSC). After data collection, all CRFs will be sent for data extraction and interpretation to the Department of Biostatistics, University of Genoa.

### Ethical aspects

The study was approved by the local Institutional Review Board (Comitato Etico, IRCCS San Martino IST, protocol no. 2/2013). The study is performed in agreement with the principles of the Declaration of Helsinki. All patients are informed about the purpose and the risks of the study and about their right to withdraw their consent at any time. Patients are only included in the study if written informed consent has been given.

## Discussion

The question of which technique should be considered the gold standard for the repair of incisional hernia remains unanswered. Currently, the topic of hernia recurrence has declined in importance because of the adoption of mesh repair, but the question of which procedure best suits the needs of the patients undergoing surgery remains open. Before a definitive conclusion can be drawn, it is imperative to correctly investigate the physiological effects of the type of repair adopted. Some premises must be considered when facing this issue. First, the patient must be considered to be a typical case with an incisional hernia and must be in their 6th or 7th decade of life. Patients at this age currently have an increased life expectancy and experience a more active lifestyle. Thus, a procedure aimed at restoring abdominal wall integrity and function may be better able to fulfill the needs of this group.

In addition, the physiological changes associated with aging have an important effect on abdominal muscles. In this period, even if not maximal, a process of lean body mass reduction starts with the impairments of mobility and total muscular strength [35]. This muscular hyposthenia could also be hampered by muscle fibrosis and atrophy occurring after incisional hernia development. This process has been recently outlined in animal models, and it is similar to what is observed in mechanically unloaded muscles [36].

The possibility of muscular structure reversal after these myopathic changes have occurred is interesting [37]. Moreover, Culbertson et al. demonstrated that a tension-free repair with mesh (bridging technique) in which the injured muscle is partially reloaded induces a better recovery of muscular structure in comparison with that of a simple repair with tension. The group postulated that “excessive tension may delay muscle recovery so there may be an optimal range of muscle length and tension during repair that results in sufficient reloading forces, while avoiding excessive tension that may delay recovery.” This interesting observation could lead to the adoption of simple bridging techniques or a hybrid Rives-Ramirez procedure in which the stability of the repair is provided by the mesh and the tension is reduced by myofascial releasing incisions.

Moreover, with the rapidly increasing use of laparoscopy, the numbers and size of incisional hernias have been reduced. Consequently, it can be postulated that two types of abdominal wall defects are currently more frequently encountered: small (<10 cm in their major diameter) primitive and incisional hernias and giant abdominal hernias. Given the aforementioned hypotheses, a patient with a small defect would receive an advantage from a simple bridging of the defect with mesh. This effect would be better indicated in comparison with an anatomical reconstruction for the inferior burden in terms of dissection, the reduced operative time and the possibility of using a less invasive approach. In contrast, a giant abdominal defect has a larger impact on the anatomy, abdominal wall compliance and the personal image of the patient. Moreover, the predicted muscular damage to the abdominal wall could be relevant. Future research needs to be conducted to determine whether, in these cases, a simple bridging would be equivalent or superior to an anatomical reconstruction and to evaluate the effects on abdominal wall function recovery.

We decided to adopt the outcome of DLL because it represents a more straightforward method to define the ability of a procedure to restore abdominal wall function. In fact, we have considered that a dynamometer is the ideal way to measure a difference because it offers a quantitative calculation of a variable that can be compared among different groups. However, as occurs for other medical variables, a significant difference could be clinically irrelevant.

